### 2.9. Randomization and blinding

After informed consent, subjects will be assigned 1:1 by computer to one of the WeChat group peer support group or the routine intervention group using a random code sequence in the order of registration. Randomization protocols are entered into the online central randomization database (www.medresman.org). Given the apparent difference in intervention strategies between the 2 groups, neither investigators nor participants were blinded; however, trial outcome assessors will be blinded.

### 2.10. Data management, informed consent and confidentiality

Data will be electronically recorded. Electronic copies will be kept on a password-protected computer in encrypted files. For 15 years, all data will be retained. The digital information will then be prepared for deletion. The questionnaires will be kept in the center’s repository for experimental research and will only be accessible to authorized staff during the course of the study. There is no personally identifying information in the participant records or surveys.

### 2.11. Sample size calculation

Overall effectiveness rate is defined as the proportion of patients whose SAS and SDS scores have reduced by more than 25%, the primary endpoint of the study. Based on previous clinical experience in our center, at the third follow-up visit, we found that the overall effectiveness rate was approximately 75% in the WeChat peer support group and about 60% in the routine intervention group. A total of 236 patients were enrolled in the study utilizing the PASS 15 procedure (NCSS, LLC. Kaysville, Utah), with a hypothesis test level of 0.05 and a test power of 0.8. After accounting for the 20% dropout rate, 296 patients with 148 in each group comprised the final sample size.

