### 2.12. Statistical analysis

The SPSS 26.0 software was used to analyze all the data (SPSS Inc., Chicago, IL). The data’s normality was evaluated using the Shapiro–Wilk test. Depending on the distribution’s normality, quantitative variables were examined using the independent samples t-test or Mann–Whitney *U* test and represented as mean standard deviation (SD) or median (interquartile range, IQR). Frequencies and percentages are used to express qualitative characteristics. Comparing categorical variables was done using the 2 test or Fisher’s exact test. In all statistics, a 2-tailed alpha of 0.05 was employed.

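### With 236 evaluable patients, the planned two-sided 0.05 test has about 70% power for 75% vs 60%, not the stated 80%

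*Protocol article*

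**What the plan says.** Section 2.11 (Sample size calculation) names the endpoint used for sizing: "Overall effectiveness rate is defined as the proportion of patients whose SAS and SDS scores have reduced by more than 25%, the primary endpoint". It assumes that "the overall effectiveness rate was approximately 75% in the WeChat peer support group and about 60% in the routine intervention group" at the third follow-up visit. The calculation is made "with a hypothesis test level of 0.05 and a test power of 0.8", and its result is given as "A total of 236 patients were enrolled in the study utilizing the PASS 15 procedure". Allowing for 20% dropout, the total becomes 296, or 148 per arm. The section does not say whether the test level is one-sided or two-sided.

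Section 2.12 (Statistical analysis) compares categorical variables by the chi-square or Fisher's exact test and sets one rule for the whole trial: "In all statistics, a 2-tailed alpha of 0.05 was employed". Section 2.9 fixes equal allocation: "subjects will be assigned 1:1 by computer". The article plans no one-sided test anywhere.

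**The concern.** The stated inputs and the stated result agree only if the 0.05 is spent in one direction, while the analysis section spends it in two. If so, the trial's claim of 80% power on its primary endpoint is wrong by about 10 percentage points, and the type II error is about 30% instead of the declared 20%.

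This affects how the result will be read. A non-significant comparison would be taken as coming from a trial with a four-in-five chance of detecting a 15-point benefit, when the chance under the planned test is nearer seven in ten.

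**Working it through.** **Inputs.** From section 2.11: p1 = 0.75, p2 = 0.60, difference 0.15, power 0.80, test level 0.05, dropout 20%. From section 2.12: two-tailed 0.05, chi-square test. From section 2.9: 1:1 allocation. Normal quantiles: 1.645 (one-sided 0.05), 1.960 (two-sided 0.05), 0.842 (80% power).

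**Step 1. Reproduce 236.** The unpooled normal approximation for two proportions is

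n per arm = (z_alpha + z_power)² × [p1(1 − p1) + p2(1 − p2)] / (p1 − p2)².

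The variance term is 0.75 × 0.25 + 0.60 × 0.40 = 0.4275, and the squared difference is 0.0225. With a one-sided 0.05:

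(1.645 + 0.842)² × 0.4275 / 0.0225 = 117.5, rounded up to 118 per arm, **236 in total**.

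This is the stated figure exactly. The one-sided pooled and arcsine versions each give 240, and the one-sided continuity-corrected version gives 266.

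**Step 2. Reproduce 296.** 118 / 0.8 = 147.5, rounded up to 148 per arm, 296 in total. The dropout step is correct, so the problem lies in the 236 alone.

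**Step 3. Apply the two-sided level of section 2.12.**

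- Unpooled: (1.960 + 0.842)² × 0.4275 / 0.0225 = 149.1, so 150 per arm, 300 in total.
- Pooled, with mean rate 0.675: [1.960 × √(2 × 0.675 × 0.325) + 0.842 × √0.4275]² / 0.0225 = 151.9, so 152 per arm, 304 in total.
- Arcsine: 304 in total. Continuity-corrected: 330 in total.

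No two-sided version comes near 236. After 20% dropout, 150 / 0.8 = 187.5 gives 188 per arm (376 in total), and 152 / 0.8 = 190 per arm gives 380 in total.

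**Step 4. Power of the planned two-sided test at 75% vs 60%.** The pooled formula is

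power = Φ{[0.15 × √n − 1.960 × √(2 × 0.675 × 0.325)] / √0.4275}.

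For n = 118 this is Φ[(1.629 − 1.298) / 0.654] = Φ(0.507) = 0.694. The exact column sums the binomial probabilities of all outcomes that the uncorrected chi-square test rejects.

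| Evaluable per arm | Pooled formula | Unpooled formula | Exact chi-square |
|---|---|---|---|
| 118 (planned after dropout) | 0.694 | 0.703 | 0.696 |
| 148 (no dropout) | 0.790 | 0.797 | 0.793 |
| 152 | – | – | 0.803 |

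One-sided, 118 per arm gives 0.800 by the same exact method, which is the power that section 2.11 claims. With a continuity-corrected chi-square test, the two-sided power at 118 per arm falls to 0.643.

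**Step 5. Difference detectable with 80% power.** Hold the control rate at 60% and 118 per arm, and test two-sided at 0.05. An intervention rate of 76.8% gives exact power of 0.800. The detectable difference is therefore 76.8 − 60 = 16.8, or about 17 percentage points, against the 15 assumed.

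**The case against.** The strongest reply is that the rates are given only as approximate. If the software was fed unrounded values, a two-sided calculation could have produced the stated size. For 76% vs 59% the two-sided pooled formula gives 117.97, so 118 per arm and 236 exactly; for 77% vs 60% it gives 234. A reader might infer from Step 1 that the calculation was certainly one-sided. The documents do not support that: section 2.11 states no sidedness, and the software output is not shown. The one-sided reading is the most natural because it returns 236 from the round figures as printed, but it remains an inference.

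This stands as a limit on the explanation. It does not rescue the power statement, because the shortfall does not depend on how 236 arose. On the printed rates and the printed two-tailed rule, 118 per arm gives about 70%. If other rates were used, section 2.11 has to show them.

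A second reply is that dropout may be below 20%. That is fair: with full retention the loss is under 1 point by the formulas and exact calculation (79.0% to 79.7%). But section 2.11 itself plans for 236 evaluable patients, and even zero loss does not reach 80%.

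Two stronger readings should be resisted. One is that dropouts would count as treatment failures, which would push power lower still; the article sets no such rule, so that scenario cannot be used to size the error. The other is that adjusting for baseline self-rating anxiety scale (SAS) and self-rating depression scale (SDS) scores would restore the lost power. The article gives nothing from which to estimate the gain. The inclusion criteria in section 2.3.1 truncate both scores from below at 50, and the endpoint is already a percentage change from baseline.

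Nor can this be left to an unseen analysis plan. It is not an omission but a conflict between figures and a rule printed in adjacent sections.

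**Conclusion.** The stated power is wrong as written. Under the article's own rates, allocation, dropout and two-tailed 0.05 rule, the trial has about 70% power for its primary endpoint (0.694 to 0.703 by formula, 0.696 exact), about 10 points below the claim. The evaluable sample is 64 to 68 patients short of what 80% power requires (300 − 236 and 304 − 236).

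The conclusion rests on taking 75% and 60% as printed, on 118 evaluable patients per arm, and on an uncorrected chi-square test; the continuity-corrected test would make it worse. That the source was a one-sided setting is likely but unproven, and the conclusion does not need it.

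**What to change.** Keep the two-sided 0.05 test of section 2.12 and correct section 2.11 to:

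- state the sidedness, the exact rates and the test option entered in the software;
- report about 70% power for 75% vs 60% with 236 evaluable patients;
- report that 80% power is available for a difference of about 17 percentage points (60% vs about 76.8%).

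If the sponsor wishes to retain 80% power for 75% vs 60%, the alternative is to re-size to 300 to 304 evaluable patients, 376 to 380 randomised. That is 80 to 84 more than the planned 296.

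Adjustment for baseline SAS and SDS may be mentioned as an optional gain of unknown size, not as a means of returning to 80%. Declaring the primary test one-sided to justify 236 would contradict section 2.12 and is not a remedy.

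The minimum change is a wording amendment. It needs no extra patients; its cost is a less favourable power statement.

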### 2.12. Statistical analysis

The SPSS 26.0 software was used to analyze all the data (SPSS Inc., Chicago, IL). The data’s normality was evaluated using the Shapiro–Wilk test. Depending on the distribution’s normality, quantitative variables were examined using the independent samples t-test or Mann–Whitney *U* test and represented as mean standard deviation (SD) or median (interquartile range, IQR). Frequencies and percentages are used to express qualitative characteristics. Comparing categorical variables was done using the 2 test or Fisher’s exact test. In all statistics, a 2-tailed alpha of 0.05 was employed.

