### 2.3. Eligibility criteria

#### 2.3.1. Inclusion criteria.

Clinically pregnant women (i.e., fetal heartbeat or gestational sac at 6–9 weeks after embryo transfer^[39]^) undergoing IVF-ET.age 18 to 49 years old.SAS standard score ≥ 50 points (i.e., mild anxiety or above); SDS standard score ≥ 50 points (i.e., mild depression or above).Patients who own electronic devices such smartphones, tablets, or computers, have Internet access, and are skilled WeChat users.Have reading, writing, and comprehension abilities.Informed consent and willing participation for WeChat group-based peer support.

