### 2.8. Outcomes

After participant enrollment, baseline evaluations will be done, then participants will have follow-up appointments at 11 to 13 weeks in the first trimester, 19 to 21 weeks in the second trimester, and 27 to 29 weeks in the third trimester. Additionally, 2 groups of people will receive electronic questionnaires for anxiety and depression levels to gauge the effectiveness of the intervention. Primary endpoint measures are improvements in anxiety and depression (i.e., overall effectiveness rate, defined as the proportion of patients with a decreases of more than 25% in SAS^[40]^ and SDS^[41]^ scores following the abovementioned intervention). At each follow-up, the anxiety and depression ratings of the 2 groups are compared horizontally, and the simultaneous effects of the 2 interventions on the subjects’ anxiety and depression are compared. The anxiety and depression ratings of the 2 groups are longitudinally compared after all the follow-up have been completed, and the effects of the 2 interventions on the participants’ anxiety and depression before and after the interventions are compared. The secondary outcomes are comparisons of pregnancy outcomes, including ectopic pregnancy, miscarriage, as well as live birth. Ectopic pregnancy is defined as the development of the fertilized egg outside the uterine cavity; miscarriage is defined as termination of pregnancy at less than 28 weeks of gestation with a fetus weighing less than 1000 g; live birth is defined as at least 22 weeks of gestation or at least 500 g.

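### The SAS and SDS score comparisons have only unadjusted independent-sample tests, which gives up precision from the baseline score and leaves no named test suited to within-woman or pooled-visit data

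*Protocol article*

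**What the plan says.** Section 2.12 (Statistical analysis) presents itself as covering the whole data set: "The SPSS 26.0 software was used to analyze all the data". For scores, the section says that "quantitative variables were examined using the independent samples t-test"; the rank-based alternative is the Mann–Whitney U test. The choice between the two follows a normality check: "The data’s normality was evaluated using the Shapiro–Wilk test". Categorical variables get a chi-square test (the symbol is lost in the text) or Fisher's exact test. No other test is listed.

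Section 2.8 (Outcomes) plans two kinds of score comparison. The first is at each visit: "At each follow-up, the anxiety and depression ratings of the 2 groups are compared horizontally". The second is over time: "The anxiety and depression ratings of the 2 groups are longitudinally compared after all the follow-up have been completed". What this second step is meant to deliver is put as follows: "the effects of the 2 interventions on the participants’ anxiety and depression before and after the interventions are compared".

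The scores are taken at baseline and at 11–13, 19–21 and 27–29 weeks; Table 1 also ticks a time point within 3 days of delivery. Entry under section 2.3.1 requires "SAS standard score ≥ 50 points" and sets the same threshold for SDS.

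The Abstract and Table 1 list anxiety and depression levels as primary. Sections 2.8 and 2.11 define the primary endpoint as the proportion of women with a fall of more than 25%, and the sample size rests on that proportion. The score comparisons are therefore treated here as supporting analyses.

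**The concern.** Every woman has a baseline SAS and SDS score before randomisation, and the same scale is repeated at each visit. A baseline measure of the outcome is usually the most useful covariate in such a trial, yet the listed tests do not use it for the score comparisons. What is at stake is wider confidence intervals than the data need to give.

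The list also does not match everything that section 2.8 could mean. If the longitudinal comparison involves before/after scores within women, or several visits pooled, a test for independent samples ignores the correlation between scores from one woman and its standard error is wrong.

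Two smaller matters follow. The Shapiro–Wilk gate lets the observed data decide whether a mean or a rank comparison is reported, and the answer may differ between visits or between SAS and SDS. And because women enter on high scores, some fall is expected in both arms by regression to the mean, so a fall within one arm does not measure an effect.

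**Working it through.** **Inputs.** From section 2.11: 236 evaluable women, 20% dropout, 296 in total. From section 2.9: 1:1 allocation. From section 2.12: two-sided 0.05. Assumed, because the article gives neither an SD nor a correlation: r = 0.3, 0.5, 0.7 between baseline and follow-up score, with equal variance at the two times.

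**The plan's own figure.** The article gives no precision or power figure for the scores. The count per arm comes from section 2.11: 236/2 = 118; 118/0.8 = 147.5, rounded up to 148; 2 × 148 = 296, which agrees. The 236 was set for 75% against 60%. With unpooled variances, n per arm = (0.75×0.25 + 0.60×0.40)(zα + zβ)²/0.15² = 19(zα + zβ)², which is 117.5 (118) at one-sided 0.05 and 149.1 (150) at two-sided 0.05. That is a separate matter; below, 118 serves only as the number of evaluable women per arm.

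**1. Between-arm comparison of follow-up scores.** Relative to the unadjusted follow-up score, ANCOVA leaves a variance of 1 − r². The unadjusted detectable difference at 80% power is (1.960 + 0.842) × √(2/118) = 0.365 SD. With adjustment it is multiplied by √(1 − r²), and the same precision needs 118 × (1 − r²) women per arm.

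| r | variance removed | detectable difference (SD) | power at 0.365 SD | women per arm for the same precision |
|---|---|---|---|---|
| unadjusted | – | 0.365 | 80% | 118 |
| 0.3 | 9% | 0.348 | 84% | 108 |
| 0.5 | 25% | 0.316 | 90% | 89 |
| 0.7 | 49% | 0.260 | 98% | 61 |

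**2. Between-arm comparison of change scores.** A change score has variance 2(1 − r) relative to the follow-up score: 1.4, 1.0, 0.6. It is valid, but at r below 0.5 it is less precise than ignoring baseline. Against change, ANCOVA leaves (1 − r²)/(2(1 − r)) = (1 + r)/2 of the variance: a reduction of 35%, 25% and 15%.

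**3. Before/after scores of the same women treated as two independent samples.** The assumed variance of the mean difference is 2σ²/n; the true one is 2σ²(1 − r)/n. The variance is overstated by 1/(1 − r) = 1.43, 2.0, 3.3. The true size of a nominal 5% test is 2(1 − Φ(1.96/√(1 − r))) = 1.9%, 0.56%, 0.03%. The test is conservative.

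**4. Three follow-up visits pooled as if from different women.** With a common between-visit correlation r, the true variance of an arm mean is 1 + 2r times the assumed one: 1.6, 2.0, 2.4. Here the error runs the other way, and the standard error is too small.

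**The case against.** A reader might infer that the plan applies independent-sample tests to the longitudinal comparison and is therefore invalid. The article does not say so. Section 2.12 assigns no test to that comparison, and section 2.8 speaks of comparing the two groups and the two interventions, which can be read as a between-arm comparison of change. Each woman then contributes one value and the t-test holds its size. This part of the objection stands: items 3 and 4 of the working describe what would happen under a different reading, not what is planned.

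A reader might also infer that the primary endpoint wastes the baseline. It does not: the responder rate is built on a percentage fall from each woman's own baseline score. Nor should the higher power of a score comparison over a responder comparison be counted here. That gain comes from not dichotomising, and section 2.8 already plans score comparisons.

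A third inference would be that within-arm improvement will be reported as efficacy. No section plans such a claim, and regression to the mean, expected alike in both randomised arms, does not bias the between-arm contrast.

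Finally, an analysis plan may exist, and a condensed article need not name every model. That would answer a complaint about silence. It does not fully answer this one, because section 2.12 is not silent: it says that it covers all the data, fixes the tests for quantitative variables, and fixes the rule for choosing between them.

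**Conclusion.** The point holds in a limited form. For the supporting SAS and SDS comparisons, the named tests are unadjusted although a baseline score is available for every woman. The type I error of a between-arm test at one visit, or on change, is intact. The loss is precision: 9% to 49% of the follow-up variance for r from 0.3 to 0.7, or 25% at 0.5. These are ranges under an assumed r, and selecting women with scores of at least 50 may pull r toward the lower end.

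The second part is a gap between sections 2.8 and 2.12: the longitudinal comparison is promised without an assigned test, and no listed test would suit it if it used within-woman or pooled-visit data. The objection to the Shapiro–Wilk gate is one of good practice; no error rate has been computed for it. None of this shows that the primary responder analysis is invalid or that the trial plans an invalid test.

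**What to change.** Keep the responder rate as the primary endpoint. In section 2.12, state that the supporting SAS and SDS scores are analysed in one of two ways: by ANCOVA at each visit with the baseline score as covariate, or by a mixed model with arm, visit, arm-by-visit and baseline score. Report the between-arm difference with its confidence interval at each visit, including 27–29 weeks. Remove the Shapiro–Wilk rule and keep the Mann–Whitney test as a sensitivity analysis. In section 2.8, say that the longitudinal conclusion rests on the between-arm contrast and not on change within an arm.

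The cost is a few sentences and slightly more analysis work on data already being collected. The mixed model brings one further obligation: the plan must say how women whose pregnancy ended before a visit are handled. This matters because miscarriage before 28 weeks is itself an outcome and the third visit falls at 27–29 weeks. ANCOVA at each visit is the simpler choice, but it too should state which women are included.

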### 2.13. Quality control and assurance

The subjects were selected in strict accordance with the protocol, and the communication with the subjects was strengthened to ensure follow-up and compliance. Each subject establishes an electronic follow-up record card to record the implementation of the intervention plan, the visit plan, the precautions during the study, the report of emergency events, etc, according to the established follow-up time and the implementation of the intervention measures. And improve the operation specifications of various instruments, and conduct regular quality control inspections on major equipment.

### 2.14. Patient and public engagement

The study comprised women who underwent IVF-ET at the Reproductive Center of Integrated Traditional Chinese and Western Medicine, Affiliated Hospital of SDUTCM, and had a confirmed clinical pregnancy as a result. No patients or members of the public were involved in the development of the study topic, study design, study conduct, interpretation of the study results, or editing and publication of the final manuscript. Their doctors will be able to communicate the results with the participants.

## 3. Discussion

Anxiety and depression are common in women who experience clinical pregnancy undergoing IVF-ET, which has a significant negative impact on both quality of life and pregnancy outcomes. How people seek care is affected by COVID-19 quarantines. As a result of poor occupancy rates per capita and unequal distribution of medical resources, traditional patient follow-up approaches are currently insufficient to handle the needs of a large number of patients.^[42]^ This study’s design is built on the WeChat group platform, which gives subjects peer support. Previous studies have shown that the WeChat group peer support can combine encouragement, support, and health education to effectively teach patients to strengthen self-management and improve living habits, effectively control overall medical expenses.^[31]^

In our study, researchers and volunteers regularly send health education texts, pictures, videos and other information through group chat or video or voice, which can break the mobile phone short message service affected by factors such as high cost, limited management, and boring text^[43,44]^ and telephone interviews^[45,46]^ and other traditional modes of information exchange. Pregnant women can interact effectively in a group conversation on WeChat. Peer support volunteers who have had children themselves can offer individualized dynamic communication to help subjects through direction and communication whenever and wherever they need it. Additionally, students can discover practical techniques and strategies for enhancing self-management, establishing a healthy lifestyle, and fostering positive outcomes. Anxiety and depression scores were calculated for 2 groups of subjects in the first, second, and third trimesters of pregnancy in conjunction with a peer support intervention in a WeChat group. Data was gathered using questionnaires, which were easy to use, cost-effective, and favorable to data collection, storage, and administration. In the future, we can work with professionals to create specialized applets that can be used throughout the assisted reproductive therapy process, giving patients affordable, practical, and efficient options.

In conclusion, we design this randomized controlled study to examine whether an intervention based on WeChat group peer support can improve anxiety, depression, and pregnancy outcomes in pregnant women following IVF-ET. This is done to ensure the medical conditions of patients under special circumstances.
